## Abstract

**Background:**

Chronic low back pain is potentially disabling for older adults, and exercise is considered the best treatment. The Pilates method and aerobic exercises have been proven to be effective in pain and function improvement in patients with low back pain, but evidence in the treatment of older adults with low back pain is scarce. Therefore, the objective of this study is to investigate the effectiveness of the Pilates method compared to aerobic exercises in the treatment of older adults with chronic nonspecific low back pain.

**Methods:**

This is a randomized controlled trial with blinded assessor, to be held in a physical therapy clinic in Sao Paulo, Brazil. Seventy four patients aged 65 to 85 years with chronic nonspecific pain will be randomized into Pilates Group (*n* = 37) with exercises based on the Pilates method and Aerobic Group (n = 37) with treadmill aerobic exercise. The primary outcomes will be pain intensity and general disability, assessed eight weeks after randomization. The secondary outcomes will be: pain intensity and general disability, assessed six months after randomization; and global perceived improvement, specific disability, dynamic balance, muscle strength (gluteus maximus, gluteus medius, and lateral hip rotators), and pressure pain threshold, assessed eight weeks and six months after randomization. Therapists and patients will not be blinded.

**Discussion:**

This study has the potential to reduce pain and, consequently, improve balance and function of older adults with chronic low back pain with both therapies. However, Pilates may be more effective because the exercises are more targeted to the trunk stabilization muscles. The results of this study may provide valuable information on the effects of Pilates and aerobic exercise in older adults with chronic low back pain and contribute to a better selection of the treatment program according to the patient preference.

**Trial registration:**

ClinicalTrials.gov NCT02729779, April 6, 2016.

**Electronic supplementary material:**

The online version of this article (10.1186/s12891-019-2642-9) contains supplementary material, which is available to authorized users.

## Background

The aging process causes functional changes such as reduction in muscle mass and strength, increase in joint stiffness, and postural instability [1]. When accompanied by chronic conditions, aging is usually associated with disability [2]. Among chronic conditions, low back pain in older adults is potentially disabling [1]. Chronic low back pain is characterized by pain or discomfort lasting for more than 12 weeks between the costal margins and lower gluteal folds, with or without symptoms in the lower limbs [3]. Chronic low back pain can be classified according to the symptomatic response, and the most common is the nonspecific low back pain [3, 4]. Approximately 36% of older adults have one episode of low back pain per year [1].

Currently, physical exercise is one of the best treatment options for patients with chronic low back pain [5], as it reduces pain and disability in the short- and long-term [4] and improves balance [6]. In relation to older adults, regular exercises can minimize the deleterious physiological effects of a sedentary lifestyle, increase active life expectancy, and prevent the development and progression of chronic diseases and disabling conditions [7]. Recently published guidelines [8] for the management of chronic pain in older adults recommend strengthening, stretching, endurance and balance training to reduce functional decline, care costs, and pain intensity. Among the types of exercises that improve chronic pain, aerobic exercises (i.e., a kind of endurance training) and the Pilates method can be treatment options.

There is reliable evidence that aerobic exercises decrease pain and improve physical and psychological functioning in patients with chronic low back pain [9]. However, despite the different pathophysiologic and clinical syndromes in older adults, most of the studies about exercise in the treatment of low back pain have been conducted in younger populations [10]. Additionally, a recent systematic review found that there is a low response rate, with estimates varying from 1.4 to 45%, in interventions based on aerobic exercises in older adults compared to young patients [11]. Nevertheless, the reasons for this poor response among older adults are not well explained, which suggests that further investigation is needed.

The Pilates method is based on six basic principles: power house, concentration, control, precision, flow of movement, and breathing [12, 13]. Pilates is prescribed as a treatment for patients with chronic low back pain because involves flexibility exercises, and strength and stability exercises of the deep abdominal muscles, with more control of the movement [14, 15]. A recent systematic review in adult patients with chronic low back pain [16] showed that the Pilates method is more effective than minimal intervention (i.e. usual care or an educational booklet) in the short- and medium-term (less than three months after randomization, and at least three months and less than 12 months after randomization, respectively) for pain and disability. Similar conclusions were shown by other recent systematic reviews [17, 18]. However, Pilates is no more effective than other types of exercise (i.e. cycling or McKenzie method) for pain and disability in the short- and medium-term [16]. A systematic review about Pilates for older adults suggests that is difficult to establish its effects because there is a lack of studies with high methodological quality [19].

Exercise is indicated for chronic pain management in older adults, and studies show positive effects of aerobic exercise [9] and Pilates [16] in the improvement of symptoms of chronic low back pain in adults. Although some studies have investigated the effects of the Pilates method on the older adult population [19] with chronic low back pain [20], there is no comparison in the literature between the Pilates method and aerobic exercises in older adults with chronic nonspecific low back pain. Moreover, randomized controlled trials including older adults with chronic low back pain are scarce, limiting the generalization of the results and generating uncertainties about the efficacy of the treatments studied in this age group [8, 21]. The purpose of this study is to evaluate the effectiveness of the Pilates method compared to aerobic exercise in improving pain and disability in older adults with chronic nonspecific low back pain.

## Methods

### Study design

This will be an assessor-blinded, 2-arm, randomized controlled trial.

### Study setting

The study will be conducted at a physical therapy outpatient clinic in Sao Paulo, SP, Brazil.

### Eligibility criteria

Older adults aged 65 to 85 years, of both sexes, with chronic nonspecific low back pain and pain intensity equal to or greater than 3 points in the last seven days in the Pain Numerical Rating Scale [22] will be included. The exclusion criteria will consider current and past conditions as follows: absolute contraindication to physical activity (changes in electrocardiogram or myocardial infarction, unstable angina, uncontrolled arrhythmia, severe symptomatic aortic stenosis, uncontrolled symptomatic heart failure, acute pulmonary embolism or pulmonary infarction, acute myocarditis or pericarditis, suspected or present dissecting aneurysm, acute systemic infection accompanied by fever, body aches, or swollen lymph nodes) [23]; severe spine disease (fractures, tumors, inflammatory diseases, ankylosing spondylitis, and radicular conditions of the spine confirmed by neurological tests); previous or scheduled surgeries of the spine; severe cardiorespiratory diseases; cancer; dependent walking (with use of walking aid or assistance from another person); physical therapy treatment for low back pain in the last six months; regular physical activity, defined as physical leisure activities for 30 min three times or more per week for the last two weeks [24]; and cognitive deficit. Cognitive deficit will be screened using the Mini-Mental State Exam, with a cut-off point of less than 13 for illiterate participants, 18 for participants with elementary education, and 26 for participants with secondary and/or higher education [25]. Eligibility criteria will be screened by a trained student by telephone, with exception of cognitive deficit and nerve root compromise, which will be screened by the blinded assessor.

### Assessment

Before assessment, written consent will be obtained from the patients. A blinded assessor, who is a physical therapist with five years of clinical experience, will evaluate the eligible participants in person. The evaluation will consist of: personal data, clinical data, and evaluation of outcomes. The initial assessment will be conducted prior to the random distribution of the patients into the treatment groups, in a reserved place. The assessment of the outcomes will be repeated eight weeks and six months after randomization in the same place. To prevent loss of follow-up, patients will be asked to be available nearly the dates of follow-ups.

The primary outcomes will be pain intensity and disability, assessed eight weeks after randomization. Secondary outcomes will be as follows: global perceived improvement, specific disability, dynamic balance, muscle strength (gluteus maximus, gluteus medius, and hip lateral rotators), and pressure pain threshold, assessed eight weeks and six months after randomization. Pain intensity and disability assessed six months after randomization will be considered as secondary outcomes too. All the questionnaires/scales used in this study show adequate measurement properties [22, 26, 27].

The pain intensity perceived by the patient in the last seven days will be evaluated by the 11-point Pain Numerical Rating Scale [22], with zero being “no pain” and 10 being “pain as bad as could be”. This scale will also be applied daily before each treatment session in relation to pain intensity in the last 24 h. The pain assessment will be conducted verbally.

Disability associated with low back pain in the last 24 h will be assessed using the Roland Morris Disability Questionnaire [22, 26, 27], consisting of 24 items that describe daily activities that patients often report difficulty performing due to low back pain. The answers are yes/no, and each affirmative answer is worth one point. The final score is calculated by adding all the points. The higher the score is, the greater the limitation.

The global perceived improvement comparing the onset of symptoms to the last few days will be assessed using the Global Perceived Effect Scale [22]. It is an 11-point numerical scale (− 5 to 5), with − 5 being “vastly worse”, 0 “no change”, and 5 “completely recovered”.

Specific disability will be assessed using the Patient-Specific Functional Scale [22], which evaluates three main activities that the patient has difficulty or inability to perform due to chronic low back pain. Each activity is evaluated on an 11-point scale, with zero being “unable to perform the activity” and 10 being “able to perform the activity at pre-injury level”. The average score for the activities will be calculated, and the higher the score, the greater the specific capacity. In addition, the detailed description of each activity will be collected to enhance the presentation of the activities that are generating disability.

Dynamic balance will be assessed by the Sit-to-Stand Test and the 10-Meter Walk Test. These tests show adequate reproducibility [28] and detect meaningful changes in physical performance measures [29]. In the Sit-to-Stand Test [28, 30], the participant will sit on a chair with a backrest and upper limbs crossed over the trunk. The test instruction is: “Please stand up and sit down five times as quickly as possible”. The time taken to perform the activity (in seconds) will be measured by chronometer. The 10-Meter Walk Test [29, 31, 32] (fast and normal) requires a 10-m straight hallway. Markers will be placed at the end of the second meter and at the beginning of the eighth meter of the path to eliminate acceleration and deceleration components. The test will be performed twice, and the participant will wear his usual footwear. First, normal walking (self-selected speed) will be evaluated, followed by fast walking (maximal speed without running). The assessor will measure the walking time by starting the stopwatch when the participants’ lower limb passes the first marker (end of the second meter) and stopping the watch as soon as they cross the second marker (beginning of the eighth meter). The verbal command for normal and comfortable walking will be: “When I say go, walk at your usual comfortable pace until I tell you to stop”. The verbal command for fast walking will be: “When I say go, walk as fast as you can, safely and without running, until I tell you to stop”.

Isometric muscle strength will be assessed using a dynamometer (Lafayette Instrument Company, Indiana, United States). The gluteus medius, gluteus maximus, and lateral hip rotators will be assessed bilaterally, since these muscles are directly related to pelvic stabilization [33]. The gluteus medius muscle will be evaluated with the participant in lateral decubitus with the test leg upwards, and hip in neutral adduction and extension [34]. Resistance to movement will be applied using a non-elastic strap and the handheld dynamometer, which will be 5 cm above the lateral epicondyle of the femur. The gluteus maximus muscle will be evaluated with the patient in the ventral decubitus position with hip neutral and knee flexed at 90 degrees [35]. Resistance to movement will be applied using a non-elastic strap and the handheld dynamometer, which will be 5 cm above popliteal region. The hip lateral rotator muscles will be assessed with the participant sitting on the stretcher with hips and knees flexed at 90 degrees, upper limbs crossed over the trunk, and hip positioned in slight lateral rotation with the medial malleolus aligned with the midline of the body [35]. Resistance to movement, using a non-elastic strap and the handheld dynamometer, will be applied 5 cm above the medial malleolus. Two submaximal force tests will be performed to familiarize the participant with each test position, followed by two repetitions with maximum isometric contraction for each muscle group and the analysis will use the average of the two maximum contractions [36]. The intrarater reliability of isometric muscle strength was tested prior to data collection and was adequate (ICC above 0.81 for the three muscular tests).

Pressure pain threshold evaluates the lowest stimulus in which a patient perceives pain [37] and will be measured using a digital pressure algometer (Somedic Inc., Hörby, Sweden®). For the algometry, marks will be made with a tape measure and pen, with the participant sitting on a chair without backrest, so that two points are marked bilaterally [38]: the first mark will be 5 cm lateral to the spinous process of L3 [39] and the second will be 5 cm lateral to the spinous process of L5 [40]. A third mark will be made on the anterior tibial muscle of the right lower limb in order to have a control [41, 42]. To measure pressure pain threshold, the circular algometer probe, which is 1 cm^2^ in area, will be positioned at a 90-degree angle on the skin and will be pressed with approximately 50 kPa/s of speed. The instruction given to the participants will be to push the button when the feeling of pressure or discomfort becomes painful. The measurements in kPa will be repeated three times at each point with a 30-s interval between measurements [43]. The average of the three measurements will be used for data analysis. If the participant does not report pain at a pressure of 1000 kPa, the test will be interrupted, and this value will be adopted as the pressure pain threshold. The intrarater reliability of the pressure pain threshold was tested prior to data collection and was adequate (ICC = 0.92).

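### Follow-up outcomes are tied to an on-site visit and the article states no remote option, although both primary scales and two secondary scales need no equipment

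*Protocol article*

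**What the plan says.** All of this is in the protocol article.

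- **Mode and place.** Under Assessment, the blinded assessor "will evaluate the eligible participants in person", and "The assessment of the outcomes will be repeated eight weeks and six months after randomization in the same place".
- **Step against missed visits.** "To prevent loss of follow-up, patients will be asked to be available nearly the dates of follow-ups". Nothing is said about what happens when a patient does not come.
- **Status of the outcomes.** "The primary outcomes will be pain intensity and disability, assessed eight weeks after randomization". At the later visit they change status: "Pain intensity and disability assessed six months after randomization will be considered as secondary outcomes too".
- **What the scales need.** For pain, "The pain assessment will be conducted verbally". For the 24-item Roland Morris questionnaire, "The answers are yes/no, and each affirmative answer is worth one point". The Global Perceived Effect and Patient-Specific Functional scales are 11-point ratings. Only the chair and walking tests, dynamometry and algometry need the site.
- **Telephone contact.** The team already uses it: "Eligibility criteria will be screened by a trained student by telephone" (Eligibility criteria), apart from the cognitive and nerve-root checks.
- **Missed treatment sessions.** Under Randomization and interventions, these get a calendar with make-up days and a limit of 10 weeks. The same section mentions free public transport for this age group.
- **Analysis.** The Statistical analysis section uses linear mixed models with group, time and their interaction, and rules out further analyses. Sample size allows for 15% loss.

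**The concern.** The primary scores share a visit with physical tests that need the site. As written, a patient aged 65 to 85 who finished treatment but is ill, away or in too much pain to travel may lose the pain and disability scores as well, although a short conversation could supply them. The plan provides for missed treatment sessions but states no equivalent for missed assessments.

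The reason for missing a visit may be the outcome itself. If patients with worse pain or disability are less able to travel, each arm looks better than it is. If this happens more in one arm, the comparison is biased too. The mixed model uses all available data and is valid if missingness depends only on what was observed. It does not remove bias from pain or disability that was never recorded. The article plans no further analysis that would show how far the result depends on this, so preventing missing scores is the main protection.

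**Working it through.** **1. Which scores a missed visit costs**

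| Outcome | Needs the site? | Status at 8 weeks | Status at 6 months |
|---|---|---|---|
| Pain (0 to 10, verbal) | No | Primary | Secondary |
| Roland Morris (24 yes/no items) | No | Primary | Secondary |
| Global Perceived Effect | No | Secondary | Secondary |
| Patient-Specific Functional Scale | No | Secondary | Secondary |
| Chair and walk tests, strength, pressure pain threshold | Yes | Secondary | Secondary |

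The first four rows could be collected by telephone. The last could not.

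**2. When patients are likely to miss a visit**

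Sessions are twice weekly for 8 weeks, with make-ups up to week 10. A patient still in treatment is therefore travelling to the clinic around the primary time point, so exposure there is probably small. At 6 months no sessions bring patients in, so exposure is probably larger, but it concerns secondary outcomes only.

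**3. Is power at stake?**

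Inputs (Sample size section): differences of 2 points (SD 2.5) and 5 points (SD 6.5), two-sided α = 0.05, power 80%, 15% loss, stated n of 34 and 37 per group.

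The plan's own figures first, with n = 2(z₀.₉₇₅ + z₀.₈₀)²(SD/difference)², divided by 0.85:

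- Pain: 25 by the normal approximation or 26 by the t-test, giving 30 or 31 per group (34 stated).
- Disability: 27 or 28, giving 32 or 33 per group (37 stated).

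The stated figures are not reproduced. They fit 85% power: the unrounded t-test n divided by 0.85 is 34.2 and 36.9. That mismatch is a separate point. Here it means only that the sample is larger than its inputs require.

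Exact t-test power with 37 randomised per group:

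| Loss | Disability | Pain |
|---|---|---|
| 5% | 89% | 91% |
| 15% | 85% | 88% |
| 25% | 80% | 83% |
| 30% | 78% | 81% |

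Power stays at 80% up to about 24 to 25% loss for disability and about 30% for pain.

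**4. Size of a possible bias (assumed inputs)**

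Suppose the lost patients in both arms are d points worse than the model predicts. Each arm's mean is then too favourable by (its loss) × d, and the comparison is biased by (difference in loss) × d. With d = 2 on the pain scale, which is an assumption:

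- loss differing by 5 points, for example 17.5% against 12.5%: 0.05 × 2 = 0.1;
- loss differing by 15 points, for example 22.5% against 7.5%: 0.15 × 2 = 0.3;
- equal loss in both arms: 0.

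Against the 2-point target this is 5% to 15%. With 37 × 0.85 = 31.45 completers per group, the standard error of the difference is 2.5 × √(2/31.45) ≈ 0.63, so 0.3 is just under half a standard error.

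**5. How many patients could be recovered?**

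The total allowance is 0.15 × 74 = 11.1 patients. It may include patients who stop treatment, from whom the plan collects nothing further. Those who stay in the trial but miss a visit are an unknown part of the 11.

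**The case against.** The strongest reply is that this is silence in a condensed article. The sentence on place describes the normal arrangement. It does not say that a non-attender is recorded as missing, may not be rebooked or may not be telephoned. Asking patients to be available around the dates suggests some flexibility, and missed-visit procedures often sit in the full protocol. This stands in part: a reader might infer that no fallback exists, and the article does not prove that. It does state the mode, the place and its step against loss, so the published rule is weak rather than merely absent.

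A reader might also infer that both visits put primary outcomes at risk. They do not, because pain and disability are primary at 8 weeks only. Nor can all 11 patients in the loss allowance be counted as recoverable.

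The bias figures are fairly challenged too. A 15-point difference at 15% overall loss means 22.5% against 7.5%, which is extreme, and even then the bias is under half a standard error. That is why they are offered only as an illustration.

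Free transport and the exclusion of people who need a walking aid or assistance make attendance easier. They do not help a patient who is ill, away or in too much pain to travel.

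Finally, telephone scores would come mainly from patients who are doing badly, so mode could be mixed up with severity. Only pain is stated to be asked verbally; how Roland Morris is administered is not given. This is a real but small cost, and a missing score is worse than one taken by telephone.

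**Conclusion.** The point holds as a cheap improvement. It is not a flaw that endangers the primary result. The article ties both follow-ups to attendance, states only a weak step against missed visits, and gives no remote route for four scales that need no equipment. Exposure is probably small for the primary outcomes at 8 weeks and probably larger for the secondary outcomes at 6 months; both judgements rest on the session schedule, not on attendance data.

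The harm would be bias from selective non-attendance. A reader might infer a loss of power, but power is about 85% or more at the planned 15% loss. The range of 0.1 to 0.3 pain points depends wholly on the assumed 2-point deficit in lost patients of both arms and the assumed 5 to 15 point difference in loss. The documents support neither figure, nor any count of patients who could be recovered. A fallback in the full protocol cannot be excluded.

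**What to change.** Add to the Assessment section, or cite there if the full protocol already has it: a patient who does not attend within a set window of the 8-week or 6-month date is telephoned by the same blinded assessor. The assessor takes pain and Roland Morris first, then the Global Perceived Effect and Patient-Specific Functional scales. Only the physical tests are left missing, and the mode (visit or telephone) is recorded for each assessment.

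The cost is one sentence, a defined window and a few calls by existing staff. The downside is a small difference in mode for a few patients, which the recorded mode makes visible.

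This does not cure a separate issue in the Statistical analysis section: outcome collection stops when a patient drops out of treatment, while the analysis is described as intention to treat. Those patients would remain without follow-up data unless that rule is also changed.
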